##### **Withdrawals from the trial and losses to follow-up**

The decision to withdraw a participant from follow-up within the trial is made only when the participant withdraws their consent to research follow-up. All reasonable attempts are made to continue to follow up all participants, including those that withdraw from intervention.

For the purposes of analysis, losses to follow-up are those missing all primary outcome scale data at all follow-up assessments, those missing all primary outcome scale data at weeks 24 and 52, or those missing all primary outcome scale data at week 52.

The numbers of withdrawals and losses to follow-up will be reported (see Comparisons of Losses to Follow-Up).

#### **
*Statistical considerations*
**

##### 

**Stratification in the analysis** The primary analysis of therapy effect will be adjusted by the factors used for stratification at randomisation (that is, centre, CDC criteria, London criteria and current depressive disorder) [12,49] and by the baseline assessment of the outcome variable.

##### 

**Method for handling centre effects** The PACE trial was designed with variation in participant outcomes between centres rather than between doctors or therapists in mind. For the primary analysis to be consistent with the trial design, the primary method for handling contextual variation in the analysis of therapy effects will be to include centre as a fixed covariate. The centre that randomises the largest number of participants will be the reference category. The centre assigned to each participant will be based on the participant’s centre at randomisation. Consideration will also be given to including centre as a random effect [50].

##### 

**Method for handling other clustering effects** Outcomes at weeks 12, 24 and 52 are nested within participants. The primary method for handling clustering associated with repeated measurements will be to fit a cluster-specific random effects model [51-53] including the participant as a random intercept, and investigating the addition of a random slope over time. Where therapy effects cannot be interpreted as population-averaged effects because outcomes are binary, a population-average (GEE) model will also be fitted.

Due to (i) the nesting of participants within therapists and doctors; (ii) the partial nesting of therapists within APT, CBT, and GET as there was no therapist involvement in SSMC; and (iii) the crossing of doctors with interventions, variation in participant outcomes between therapists, and in intervention effects between SSMC doctors, are recognised to be potential sources of clustering in this trial [54]. The data structure envisaged in the design (Figure 2) differs from that observed in practice due to a number of planned deviations resulting from unavoidable therapist absences (section 8.6 of Protocol v5.2). To summarise:

a. Local centre cover delivered by a PACE therapist of the same discipline working in a nearby centre will mean that some therapists will be crossed with centres.

b. Distant therapy delivered by a PACE therapist of the same discipline means that participants will not always be seen by a single therapist.

c. Cross-cover therapy delivered by a PACE therapist of a different discipline means that participants will not always be seen by a single therapist and some therapists may be crossed with the therapies.

d. Recruitment of a replacement therapist means that more than one therapist per centre may deliver each therapy.

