**Method for handling dropouts and missing data** Data are missing completely at random (MCAR) when they represent a simple random sample of the complete sample and the missing data mechanism is independent of all observed and unobserved variables. The assumption that data are missing at random (MAR) is reasonable when missing data represent an identifiable stratified sample of the complete sample and the missing data mechanism is dependent only on other known and observed variables. Data are missing not at random (MNAR) where missing data represent an unidentifiable stratified sample of the complete sample and the missing data mechanism depends on measured and unmeasured variables. The model describing the missing data mechanism will take any clustering effects into consideration. The planned strategy for handling missing data at the item [56] and scale [57] levels will depend on whether the amount of item-missing data observed is minimal. Within practical constraints it will be assumed that data are missing at random (MAR) conditional on the variables included in the substantive model.

##### 

**Missing item data** To ensure the same strategy is followed across all scales reported in the principal paper(s) any guidance given by authors of validated questionnaires will be superseded by the strategy outlined here. Where item-missing data are considered minimal (defined here as no more than 10% of participants with any missing item data across visits where collected or where no more than 20% of the items within a scale are missing within participants), prorating (that is, mean imputation across items within a scale, or subscale where scales are formed of subscales, for each visit and participant) [56] will be used. The focus will instead be on handling scale-missing data. Any bias or underestimation of variance of scores associated with prorating is anticipated to be negligible where item-missing data are minimal [56]. We will report the amount of missing item data by the percentage of participants who have more than 10% item missing data for each scale reported.

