**Method for handling compliance** The primary analysis will be based on the intention-to-treat principle which compares the randomised intervention policies rather than the interventions *per se*[48]. Interpretation of the extent to which intervention effect estimates reflect the effects of the intervention described in the protocol requires analyses focusing on the effects of the interventions received rather than the interventions prescribed. It is recognised that per-protocol analyses have a number of limitations, most importantly, selection biases resulting from participants who are excluded not being a simple random sample of those randomised. As such, discrepancies between the conclusions of an intention-to-treat analysis and a per-protocol analysis may not reflect discrepancies between the effects of the intervention prescribed and the intervention received. Acknowledging these and other limitations, a per-protocol analysis will serve as the primary sensitivity analysis investigating the robustness of the conclusions of the primary analysis to assumptions about departures from the randomised intervention policies.

#### **
*Descriptive analyses*
**

##### 

**Description of available data** The patterns of availability of baseline and follow-up data will be summarised overall and separately for the four interventions and for each assessment visit at the scale level. If one or more case report forms (CRFs) are available for a particular visit then the visit will be regarded as available. If one or more (non-administrative) items are available then the scale will be regarded as available. Availability of baseline and follow-up data will be summarised with differentiation of fully, or partially completed measures from those completely missing, or with sketchy detail.

The timing of baseline and follow-up data will be summarised overall and by intervention for each assessment visit in terms of the median (lower quartile, upper quartile, minimum and maximum) number of days from randomisation and the proportion falling outside guideline timeframes. Histograms of distributions will also be examined. Where assessments for a particular visit are carried out on more than one date, the timing of CFQ and SF-36PF assessments will be used to summarise visit timing. The extent to which visits are carried out on more than one date will be examined together with any further relevant details.

##### 

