##### **Efficacy outcomes**

##### 

**Definition of outcome measures (including trial periods)** All secondary efficacy outcomes are defined separately at weeks 12, 24 and 52 unless specified otherwise (see Baseline and Outcome Measures). The PACE Scoring Protocol outlines in detail the process for calculating scores from questionnaire items and variables from case report forms. Participant-, therapist- and SSMC doctor-rated CGI are defined as ordinal variables with three categories. Participant satisfaction is defined as an ordinal variable with seven categories. The anxiety and depression subscale scores of the HADS, the Walking Test, and the total score of the Work and Social Adjustment scale are all continuous variables. However, the distribution of these is not pre-specified with the possibility that some or all may be skewed and the Walking Test may be bimodal. The number of CDC symptoms is a count variable and CDC Symptoms (1) and (8) are binary variables.

##### 

**Descriptive statistics for outcome measures** The distributions of all secondary efficacy outcomes will be presented in histograms (continuous/count) or bar charts (ordinal/binary) both overall and by intervention at each assessment point. A single table will be produced including summary statistics for all secondary efficacy outcomes by intervention and assessment point. Numbers (and percentages) or means (and standard deviations, minimums and maximums) or medians (and inter-quartile ranges, minimum and maximums) will be presented as appropriate. Summary statistics will be further plotted using line graphs for each outcome across time by intervention. The anticipated profiles have not been specified in advance. Potential variability in secondary efficacy outcomes between therapists and between doctors will be investigated using an approach similar to that outlined for the primary outcomes.

##### 

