**Primary analysis (including method of analysis)** The primary analyses addressing secondary objective (3) will involve the secondary efficacy outcomes and will be based on the intention-to-treat principle. Participant will be included as a random intercept (investigating adding a random slope on time), time (investigating the possibility of linearising this effect across 12, 24 and 52 weeks) and the associated baseline variable as fixed effects and centre, CDC criteria, London criteria, and Current Depressive Disorder as fixed indicator variables. Participant-rated CGI and the participant satisfaction will be analysed using mixed-effects ordinal logistic regressions. The anxiety and depression subscale scores of the HADS, number of CDC symptoms, the Jenkins sleep scale total score, the Walking Test, and the total score of the Work and Social Adjustment scale will be analysed using mixed-effects linear regressions, unless there is evidence to suggest that these outcomes are skewed/bimodal, in which case transformation and bootstrapping will be investigated. CDC Symptoms (1) and (8) will be analysed using mixed-effects logistic regressions. The intervention and time-by-intervention contrasts fitted for the primary outcomes will be extracted for each secondary efficacy outcome as outlined in the analyses of the primary outcomes.

##### 

**Baseline adjustment** The same as that outlined for the primary outcomes

##### 

**Model assumptions checks** The following will be checked as described for the primary analysis of the primary outcomes

1. Independence of residuals

2. Distribution of residuals

3. Equal variance of residuals

4. Distribution of random effects (as appropriate)

5. Absence of an intervention-by-centre interaction

6. Extreme outliers and points with high leverage

##### 

**Other analyses supporting the primary analysis** Sensitivity analyses investigating the robustness of the conclusions of the primary analyses of the secondary efficacy outcomes will be less extensive than those described for the primary outcomes unless concern is raised by those carried out for the primary outcomes.

##### 

**Safety outcomes** These analyses will be based on the safety sample (see Trial Samples).

##### 

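### The rule that adds a population-averaged model covers binary outcomes only and so misses the ordinal logistic analyses of participant CGI and satisfaction

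*SAP article*

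**What the plan says.** Under Method for handling other clustering effects, the main approach to repeated measurements is a cluster-specific model "including the participant as a random intercept, and investigating the addition of a random slope over time". The same paragraph then gives the exception: "Where therapy effects cannot be interpreted as population-averaged effects because outcomes are binary, a population-average (GEE) model will also be fitted".

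Under Efficacy outcomes, the outcome types are fixed: "Participant-, therapist- and SSMC doctor-rated CGI are defined as ordinal variables with three categories", and "Participant satisfaction is defined as an ordinal variable with seven categories". The models follow: "Participant-rated CGI and the participant satisfaction will be analysed using mixed-effects ordinal logistic regressions". The outcomes there that plainly meet the binary condition are two single symptoms: "CDC Symptoms (1) and (8) will be analysed using mixed-effects logistic regressions".

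Three other places bear on the point:

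- Method for handling compliance says that the primary analysis "compares the randomised intervention policies rather than the interventions" themselves.
- Method for handling multiple comparisons and multiplicity bases interpretation on the size and precision of the differences between interventions. It makes CGI the only secondary outcome with Bonferroni-adjusted P-values.
- Among the analyses supporting the primary analysis of fatigue and disability, a categorical CGI analysis lists three categories (response, no response, deterioration) but names mixed-effects logistic regression, without the word ordinal.

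**The concern.** The plan accepts that a participant random-intercept model need not give a population-averaged effect, and it provides a remedy. It ties the remedy to the number of categories, whereas the cause is the non-linear link. A cumulative-logit model with a participant random intercept behaves in the same way at every cut-point: its odds ratio is conditional on the participant's own intercept and lies further from 1 than the odds ratio between the randomised groups. CGI and satisfaction have the property that the rule was written for, but they do not trigger it.

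What is at stake is the size of an effect. Secondary objective 1 asks whether the pattern on the primary outcomes is replicated on CGI. The plan judges results by magnitude, and its intention-to-treat question is about policies, that is, about groups. If the only adjusted CGI estimate is participant-specific and it is read as the group effect, the effect will look larger than it is. By how much depends on a variance component that has nothing to do with treatment.

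**Working it through.** **1. Does the rule reach these outcomes?**

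| Outcome | Type in the plan | Model | Population-averaged model triggered? |
|---|---|---|---|
| Fatigue, physical function | Continuous | Linear mixed | Not needed (identity link) |
| CDC symptoms (1) and (8) | Binary | Mixed logistic | Yes |
| Participant CGI, Efficacy outcomes | Ordinal, 3 categories | Mixed ordinal logistic | No |
| Participant satisfaction | Ordinal, 7 categories | Mixed ordinal logistic | No |
| Participant CGI, supportive analysis | 3 categories listed | Mixed logistic | Unclear |

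The optional further models in the clustering section concern therapists and doctors and do not fill the gap.

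**2. How large could the gap be?** The plan states no figure to reproduce and gives no random-intercept variance. The latent intraclass correlation (ICC) between visits is therefore an assumption, taken over a range.

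- Random-intercept variance = (π²/3) × ICC/(1 − ICC).
- Participant-specific log OR ≈ population log OR × √(1 + 0.346 × variance).

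| Assumed ICC | Variance | Multiplier of log OR | Population OR 2.0 appears as |
|---|---|---|---|
| 0.1 | 0.37 | 1.06 | 2.1 |
| 0.3 | 1.41 | 1.22 | 2.3 |
| 0.5 | 3.29 | 1.46 | 2.8 |
| 0.7 | 7.68 | 1.91 | 3.8 |

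For example, at ICC 0.5: √(1 + 0.346 × 3.29) = √2.138 = 1.46, and 2.0 to the power 1.46 is about 2.8.

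**3. Check by numerical integration over the random intercept.** The response rates come from the plan's sample size section and serve only as an illustration.

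- 10% versus 25% is a population OR of (0.25/0.75)/(0.10/0.90) = 3.00. The matching participant-specific OR is 3.17, 3.70, 4.72 or 7.45 at ICC 0.1, 0.3, 0.5 or 0.7.
- 25% versus 50% is also a population OR of 3.00. The participant-specific OR is 3.27, 4.02, 5.40 or 9.13.

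For a population OR of 3.00 the closed form gives 3.00 to the powers 1.06, 1.22, 1.46 and 1.91, or about 3.2, 3.8, 5.0 and 8.2. These lie between the two exact sets, so the approximation is good enough here. The participant-specific OR is further from 1 in every case.

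**4. The reverse direction for a three-category outcome.** Assume a participant-specific cumulative OR of 3, with 25% positive and 10% negative change in the reference arm. The population ORs at the two cut-points are:

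| Assumed ICC | Positive versus rest | Not negative versus negative |
|---|---|---|
| 0.3 | 2.39 | 2.69 |
| 0.5 | 2.06 | 2.36 |
| 0.7 | 1.74 | 1.96 |

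Proportional odds given the random intercept therefore does not carry over to the population scale: there is no single marginal odds ratio to report.

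**The case against.** Several stronger readings are tempting, and the document does not support them.

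- **That the planned odds ratio is wrong or overstates the effect.** It is a valid estimate of a participant-specific quantity. It overstates only when read as the contrast between randomised groups.
- **That the multiplicity-controlled test of CGI is compromised.** The null hypothesis is the same on both scales, so the P-values and the 0.05/5 = 0.01 threshold should change little. Objective 1 also asks about a pattern of results, which depends in part on direction and consistency.
- **That CGI gets only participant-specific odds ratios anywhere in the plan.** The supportive CGI analysis uses the same model name as the binary CDC symptoms. If it is run as a binary split, the existing rule adds a GEE model. The three listed categories point the other way, so the text is ambiguous. The plan also provides summary statistics by arm and visit, including percentages where appropriate, so crude marginal results should be visible.
- **That the gap is as large as the upper rows suggest.** No ICC is given, and the relevant variance is what remains after covariate adjustment. At ICC 0.1 the gap is slight.
- **That the GEE remedy contradicts the missing-data assumption.** The plan says that "it will be assumed that data are missing at random (MAR) conditional on the variables included in the substantive model", and unweighted GEE generally needs more than this when dropout depends on earlier outcomes. But GEE is fitted in addition to the likelihood-based model, and after multiple imputation it need not have this weakness. The point is secondary and bears only on how to obtain the marginal estimate.

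What stands is narrower. The ordinal analyses under Efficacy outcomes trigger no population-averaged model. Crude percentages are unadjusted and are not a planned contrast with a CI.

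**Conclusion.** The point holds as an inconsistency in the plan's own principle. The remedy is triggered by binary outcomes, but the ordinal logistic models for participant CGI and satisfaction need it for the same reason. As written, those analyses produce no adjusted population-averaged contrast, in a plan that interprets by size of effect and targets the randomised policies.

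The consequence concerns magnitude and interpretation. It does not concern error rates, and the linear models for fatigue and physical function are untouched. The difference runs from slight at low within-participant correlation to nearly a doubling of the log odds ratio at ICC 0.7. Those figures rest on an assumed ICC and a normally distributed random intercept. If a random slope is added, the variance that matters is the total random-effect variance at week 52.

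**What to change.** 1. In Method for handling other clustering effects, extend the condition to binary or ordinal outcomes.
2. For participant CGI and satisfaction, report a population-averaged contrast at week 52, with a CI, for each planned comparison. One way is to average the fitted mixed model's predicted category probabilities over the random effects and covariates, arm by arm. This works from the same likelihood fit and so keeps its missing-at-random assumption.
3. Present the result as differences in proportions (for CGI, positive change and negative change) or as cut-point-specific marginal odds ratios, not as one marginal odds ratio.
4. In the supportive CGI analysis, state whether the model is ordinal or binary and, if binary, how the three categories are split.
5. GEE may be kept as a check.

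The cost is a small wording change and a post-estimation step, with no new data. The reported effect will be closer to the null, and so less favourable, than the participant-specific odds ratio.

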**Figure 2 F2:**
[figure not shown]
Data structure envisaged in the design.

It is also possible that participants may be seen by more than one SSMC doctor over the course of the trial.

These deviations are anticipated to affect less than 10% of the trial participants. We will initially assume independence of outcomes within therapists/doctors in the primary analysis. Two further analyses are planned, using two-level heteroscedastic models assuming a fully nested design [54], with clusters based on i) the main care provider and ii) the pair comprising the main therapist and the main doctor to assess the robustness of the model to the assumption of independence.

If no clustering is found in (i) supporting the conclusions of the primary analysis, then (ii) will not be performed. The ‘main care provider’ is defined as the therapist or doctor providing the largest number of trial therapy sessions for each participant. As such, the main care provider is likely to be a therapist for APT, CBT, and GET and a doctor for SSMC. To be explicit, if the doctor provides more sessions than the therapist in APT, CBT or GET then the doctor is the main care provider (see Departures from Randomised Intervention Policy). If there is a tie in number of sessions delivered by two care providers the main care provider will be the one who delivered the earlier sessions.

In summary, three analyses are planned: 1) without accounting for therapist effect/clustering, 2) accounting for main care provider, and 3) accounting for both the main therapist and main doctor for each participant. The third will not be done if the second shows no clustering effects.

An analysis accounting for the effect of clustering on secondary outcomes will be considered.

Any differences in the point estimates, confidence intervals (CIs) or conclusions will be reported. Any problems encountered in fitting these models will be reported and the scope of the analyses will be restricted; the weights used within the multiple membership model [55] will be determined by the proportion of participants treated by each therapist/doctor.

Additional models to explore or take account of complex clustering effects may also be fitted; if so, the motivation for these will be reported together with their results.

##### 

**Method for handling dropouts and missing data** Data are missing completely at random (MCAR) when they represent a simple random sample of the complete sample and the missing data mechanism is independent of all observed and unobserved variables. The assumption that data are missing at random (MAR) is reasonable when missing data represent an identifiable stratified sample of the complete sample and the missing data mechanism is dependent only on other known and observed variables. Data are missing not at random (MNAR) where missing data represent an unidentifiable stratified sample of the complete sample and the missing data mechanism depends on measured and unmeasured variables. The model describing the missing data mechanism will take any clustering effects into consideration. The planned strategy for handling missing data at the item [56] and scale [57] levels will depend on whether the amount of item-missing data observed is minimal. Within practical constraints it will be assumed that data are missing at random (MAR) conditional on the variables included in the substantive model.

##### 

**Missing item data** To ensure the same strategy is followed across all scales reported in the principal paper(s) any guidance given by authors of validated questionnaires will be superseded by the strategy outlined here. Where item-missing data are considered minimal (defined here as no more than 10% of participants with any missing item data across visits where collected or where no more than 20% of the items within a scale are missing within participants), prorating (that is, mean imputation across items within a scale, or subscale where scales are formed of subscales, for each visit and participant) [56] will be used. The focus will instead be on handling scale-missing data. Any bias or underestimation of variance of scores associated with prorating is anticipated to be negligible where item-missing data are minimal [56]. We will report the amount of missing item data by the percentage of participants who have more than 10% item missing data for each scale reported.

The amount of item-missing data is expected to be minimal. However, if this is not so for any outcome scale then multiple imputation [58,59] at the item-level will be the primary method used. Items will be imputed 100 times [60] separately for each scale (with the exception of the CFQ and SF-36PF, which will be imputed simultaneously). All of the other items for that scale across all time points (including baseline), scores (overall and any subscales) across all time points (including baseline), the four stratification factors at randomisation, randomised intervention, main therapist, and main SSMC doctor will be included in the imputation model.

##### 

**Missing scale data** Missing baseline scale data are not an issue for the primary analysis of efficacy; no missing data are expected for the stratification factors. Where the CFQ or SF-36PF is missing at baseline they will be replaced by the relevant scale at screening. There is specific guidance for missing baseline scale data, and this will be followed [61]. That is, we will use mean imputation of baseline variables assuming baseline and outcome are correlated less than 0.6.

Where the amount of item-missing data is considered minimal, missing outcome scale-data will be handled within the primary analysis by maximum likelihood [57,62] under a similar model for the missing data mechanism assumed for missing item data (see section above). We will report the amount of missing scale data by the percentage of participants who have more than 10% missing item data for each scale reported.

##### **
*Loss to follow-up*
**

Some participants will withdraw from follow-up during the trial, and for these it may be more appropriate to assume data are missing not at random (MNAR). Where more than 10% of randomised participants are lost to follow-up, the impact of this will be investigated in a sensitivity analysis using the weighting approach described by Carpenter, Kenward and White [63] if multiple imputation is the primary method, or comparing selection model and pattern-mixture model therapy effect estimates [64] where maximum likelihood is the primary method.

##### **
*Method for handling multiple comparisons and multiplicity*
**

The overall probability of falsely claiming a statistically significant result increases when multiple significance tests (or equally CIs) are interpreted simultaneously. Multiplicity considerations arise in this trial from the presence of (i) multiple outcomes, (ii) multiple intervention comparisons, and (iii) multiple analyses.

The strategy for adjusting, presenting and interpreting the results is set out below.

Multiplicity adjustments will be made as follows:

1. The following five comparisons will be made using two-sided hypothesis tests (alpha = 0.05) at 52 weeks: APT versus SSMC, CBT versus SSMC, GET versus SSMC, CBT versus APT, GET versus APT.

For the co-primary outcomes, fatigue and disability, and for the secondary outcome, the participant-rated CGI, *P*-values will be presented unadjusted for multiplicity.

2. In addition Bonferroni adjustment (0.05/5) will be applied separately to each of the three outcomes to control the outcome-wise type I error rate at 5%.

3. No adjustment will be made for any sensitivity analysis as their purpose is to increase confidence in the results obtained from the analysis nominated as primary [26].

4. No adjustment will be made within the principal paper(s) for other analyses including those for safety, secondary outcomes (except the CGI) [26], and health economics.

Presentation will occur as follows:

1. All analyses undertaken will be reported as far as practical (regardless of statistical significance) [65].

2. Estimated effects will be presented with unadjusted 2-sided 95% CIs and *P*-values.

3. *P*-values adjusted for multiplicity will also be presented and explained.

Interpretation will be done as indicated below:

1. Marginal interpretation of the results will be of primary interest and will be based on the size and precision of the observed differences between interventions with reference to point estimates and unadjusted 95% CIs.

2. Intervention recommendations will also take into consideration the consistency of effects

a. across any supportive intervention contrasts,

b. across sensitivity analyses, primary outcomes and time points,

c. across efficacy, safety and cost analyses, and

d. with the results of previous studies, and clinical and consumer opinions.

##### 

**Method for handling compliance** The primary analysis will be based on the intention-to-treat principle which compares the randomised intervention policies rather than the interventions *per se*[48]. Interpretation of the extent to which intervention effect estimates reflect the effects of the intervention described in the protocol requires analyses focusing on the effects of the interventions received rather than the interventions prescribed. It is recognised that per-protocol analyses have a number of limitations, most importantly, selection biases resulting from participants who are excluded not being a simple random sample of those randomised. As such, discrepancies between the conclusions of an intention-to-treat analysis and a per-protocol analysis may not reflect discrepancies between the effects of the intervention prescribed and the intervention received. Acknowledging these and other limitations, a per-protocol analysis will serve as the primary sensitivity analysis investigating the robustness of the conclusions of the primary analysis to assumptions about departures from the randomised intervention policies.

#### **
*Descriptive analyses*
**

##### 

**Description of available data** The patterns of availability of baseline and follow-up data will be summarised overall and separately for the four interventions and for each assessment visit at the scale level. If one or more case report forms (CRFs) are available for a particular visit then the visit will be regarded as available. If one or more (non-administrative) items are available then the scale will be regarded as available. Availability of baseline and follow-up data will be summarised with differentiation of fully, or partially completed measures from those completely missing, or with sketchy detail.

The timing of baseline and follow-up data will be summarised overall and by intervention for each assessment visit in terms of the median (lower quartile, upper quartile, minimum and maximum) number of days from randomisation and the proportion falling outside guideline timeframes. Histograms of distributions will also be examined. Where assessments for a particular visit are carried out on more than one date, the timing of CFQ and SF-36PF assessments will be used to summarise visit timing. The extent to which visits are carried out on more than one date will be examined together with any further relevant details.

##### 

**Description of missing data** Where available, the reasons for missing baseline and follow-up data will be summarised overall and by intervention at the visit and scale levels. This will be done using relevant information included in the comments fields of the database. It is anticipated that such information will be available principally for visit and scale missing data.

Where the level of item-missing data is borderline between ‘minimal’ and ‘important’ (see Methods for Handling Dropouts and Missing Data), the appropriateness of prorating will be evaluated using the checks outlined by Fayers *et al*. [56]. Assumptions regarding the nature of the missing data mechanism (that is, MAR as compared to MCAR and MAR, conditional on the variables included in the substantive model as compared to additional variables) will be evaluated by looking descriptively at the statistical associations between whether or not data is missing and any potential predictors, including those generated by looking at the comments fields or the data.

##### 

**Participant flow** Participant throughput will be summarised in a CONSORT diagram [28] including the stages of enrolment, allocation, follow-up and analysis (see Figure 3). Where available, similar summary information will also be provided on the flow of therapists and doctors from recruitment to analysis [66]. In addition to the median, lower quartile, upper quartile minimum and maximum, the arithmetic, harmonic and minimum-variance mean cluster sizes together with the standard deviation will be tabulated by intervention as these may be useful for calculating the design effect where cluster sizes are variable in size [67,68].

